#### Telephone follow-up

Follow-up telephone calls once a week for 3 weeks by the research assistants will be arranged between the fifth and seventh sessions for participants in the mindfulness group when they have learned the basic mindfulness skills after the four face-to-face sessions to monitor the progress and adherence to home practice of the MBCT participants. To maintain intervention consistency, the research assistants will be reminded not to provide any suggestions or encouragement for the caregivers over the telephone. The telephone follow-up content will be adopted from 3 questionnaires (forms A–C). Form A consists of simple questions such as the frequency of practice and the general learning experience, and form B consists of the same questions as in form A plus some other questions to explore the participants’ application of the practice of mindfulness in daily life. Form C consists of all the questions from forms A and B plus some more questions to explore and monitor the participants’ response to stress after practicing mindfulness and how the participants would apply mindfulness techniques when facing future obstacles.

#### Intervention fidelity

Intervention fidelity checking will be conducted weekly during the intervention period based on the intervention fidelity checklist which covers the rundown and activities of each mindfulness session. The checklist followed the MBCT protocol and was reviewed by an experienced, qualified MBCT teacher. All the intervention sessions will be audio recorded and the investigator will immediately listen to the content after each lesson and check against the fidelity checklist. Achieving a fidelity rate of > 90% will be considered acceptable based on the recommendations of the NIH Behavior Change Consortium [27]. If any missing items in the sessions are found, the interventionist will add it back in the following session. Monthly quality control meetings with all research personnel (the MBCT instructor and research assistants) will be arranged to evaluate their instruction/facilitation skills in this study.

There will be only one interventionist in this study delivering all the modified MBCT sessions and thus variations in the implementation of the interventions will be minimized. The interventionist will be a qualified MBCT teacher who has experience in conducting a similar program to caregivers of PWD. Thus, the interventionist should have a good understanding about the characteristics as well as the difficulties of caregivers for PWD. Since the MBCT protocol has been modified from the original design, the investigators will discuss and clarify with the interventionist about the changes in the protocol and ensure the program is following the outline.

#### Control group (SIRE on dementia care)

The participants of the control group will be provided with chances to socialize and interact with other participants via the SIRE program. The SIRE program has been developed for this study and the aim is to control the socialization and interaction effect as it may mask the effects of the modified MBCT in stress reduction, making it difficult to draw a meaningful conclusion about the effectiveness of the modified MBCT for family caregivers of PWD. The SIRE program consists of seven sessions, with the same group size, duration, and frequency of sessions as the MBCT group, including education sessions on dementia care, caregiver skills training, and group sharing on caregiving tasks. The program will be delivered by an experience nurse in dementia care.

### Data collection procedure

All outcome assessments will be collected by the research assistants, who will be blinded to the group allocation, within 1 week after the completion of the intervention (T1) and 6 months after the intervention (T2). A Data Monitoring Committee will be formed to ensure the safety of the participants and their protection from harm as a result of the intervention. No harmful effect of MBCT was reported in previous studies. The potential harm to the participants may be some negative emotions being triggered when the caregivers share their own personal experience. If this happens, we will refer them to professionals such as social workers or nurses for further assessment. In order to minimize the risks, the interventionist will closely monitor the emotional state of the caregivers. The research assistants and outcomes assessors will also be trained to identify emotional distress of the caregivers and handle emergency situations such as suicide ideation among the caregivers.

### Outcome measurement

A variety of outcomes (described below) will be measured at baseline (T0), immediately after the intervention (T1), and at 6-month follow-up (T2). The FFMQ will be measured in the intervention group only and the baseline measurement will be conducted at the end of the third session (the mid-point of the intervention) when they have learned most of the basic skill and principle of mindfulness [28], followed by measurement immediately after the intervention (T1) and at 6-month follow-up (T2). The previous study showed that the participants’ level of mindfulness started to increase after the mid-point of the intervention, and the remaining sessions after the mid-point will further help the participants to cultivate a mindfulness attitude [29]. All assessments will be carried out by independent outcomes assessors who will be blinded to the group assignments. Sociodemographic data of the subjects will be obtained at baseline (before randomization and within 2 weeks before the implementation of the intervention) to assess the comparability of the groups and thus external validity of the results. Information such as caregiver relationships, time of caring for PWD, employment status, use of caring service, and so on, will be obtained.

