### Hypotheses of the study

Participants in the intervention group will have better improvement than the control group after the seven-session, 10-week modified MBCT intervention immediately after the intervention (T1) and/or at 6-month follow-up (T2) in terms of the following hypotheses: 1) significantly greater reduction of stress (primary outcome); and 2) significantly greater improvement in the secondary outcomes, namely depression, anxiety, resilience, burden, health-related quality of life, and the behavioral and psychological symptoms of the care recipient.

In addition, there are two hypotheses to facilitate the explanation of the positive changes in the modified MBCT group: 1) there will be significant positive correlations between the levels of mindfulness of the caregivers (total score of five facets of mindfulness) and the improvement in their stress, depression, anxiety, burden, resilience, health-related quality of life, and/or behavioral and psychological symptoms of the care recipient; and 2) increased use of all facets or individual facets of mindfulness skills of family caregivers will be significantly and positively correlated with the improvements in their psychological outcomes (stress, depression, anxiety, burden, resilience, and/or health-related quality of life).

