### Data analysis plan

IBM SPSS 23.0 software will be used for the data analysis. The Kolmogorov–Simonov test will be used for checking normality. To ensure the similarity of the subjects in the two groups (modified MBCT and SIRE) at baseline, the demographics, adherence rate, frequency of mindfulness practice, and the outcome measurements will be compared by using a *t* test for continuous variables and a Chi-square test for categorical variables. Covariates will be controlled in the main analyses if a significant difference of variables is found at baseline. Both per-protocol (PP) and intention-to-treat (ITT) analyses will be performed. In the PP population, we will include the subjects who attend > 70% of the intervention sessions. A sensitivity test will be performed to compare the differences between the ITT and PP results. The aim of conducting both ITT and PP analyses is to uncover factors affecting the use and effectiveness of the modified MBCT, such as noncompliance and acceptability [48].

Descriptive statistic will be used to analyze the recruitment rate, attrition rate, duration, patterns, and consistency of the participants practicing mindfulness to indicate the acceptability of the MBCT. Mixed multivariate modeling (MANOVA) tests will be adopted to investigate the between-group effect (groups: modified MBCT and SIRE), the within-group effect (times: T0, T1, and T2), and the interaction time effect of group by time effect (group × time) on all of the outcome variables including PSS, HADS-A, CESD, ZBI, BRS, NPI-Q, and SF-12v2, and the process indicator (FFMQ). Correlation checking by Pearson’s product moment correlation of all the psychological outcomes including PSS, HADS-A, CESD, ZBI, BRS, NPI-Q, SF-12v2, and the process indicator (FFMQ) at baseline will be performed. If the correlation is too strong (Pearson’s *r* > 0.6), which may result in multicollinearity and violation of the assumption of mixed repeated MANOVA, then two-way repeated ANOVA and Bonferroni’s adjustments will be adopted to prevent a type I error [49]. Post-hoc pairwise comparisons using Tukey’s Honestly Significant Difference (HSD) will be performed to examine the significant difference in the outcomes.

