The Pearson’s correlation coefficient (*r*) (or Spearman’s correlation coefficient, as appropriate) will be adopted for the following variables to examine their correlations:The FFMQ total score as the independent variable and the outcome measurements including mean scores of stress, depression, burden, and anxiety as the dependent variables.The subscale (each facet) of the FFMQ score as the independent variable and the outcome measurements including mean scores of stress, depression, burden, and anxiety as the dependent variables.The duration of mindfulness practice as the independent variable and the level of mindfulness as the dependent variable.

The degree and pattern of missing data will be analyzed using SPSS Statistics Missing Values. If the missing value is a small amount (< 20%) and randomly distributed, the last observation carried forward (LOCF) method will be adopted to replace the missing data [50, 51]. However, if the missing values are not randomly distributed, multiple imputations will be adopted. This will create several different plausible imputed datasets and the results obtained from each of the sets will be appropriately combined [52].

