## Limitations

We are conducting this study in nongovernmental organizations offering support for the family caregivers, which may limit the ability to generalize the findings to all community-dwelling caregivers. There is also a chance of bias since the participants are aware of the intervention. Thus, the level of mindfulness will be measured to understand the mediating effect or active components of the MBCT contributing to any significant benefits for the participants.

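### The FFMQ is collected in the MBCT arm only, first after session 3, yet the analysis plan enters it in the group × time model and the baseline correlation check

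*Protocol article*

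**What the plan says.** Under Outcome measurement, the general schedule is that outcomes "will be measured at baseline (T0), immediately after the intervention (T1), and at 6-month follow-up (T2". The FFMQ is an exception: "The FFMQ will be measured in the intervention group only and the baseline measurement will be conducted at the end of the third session". That is session 3 of 7, described as the point "when they have learned most of the basic skill and principle of mindfulness". The section explains the choice by reporting that mindfulness began to rise after the mid-point in an earlier study. T1 and T2 readings follow, again in the MBCT arm only.

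The Data analysis plan tests a between-group effect, a time effect over T0, T1 and T2, and "the interaction time effect of group by time effect (group × time". These are to be examined "on all of the outcome variables including PSS, HADS-A, CESD, ZBI, BRS, NPI-Q, and SF-12v2, and the process indicator (FFMQ". The same variables, FFMQ included, go into a Pearson correlation check at baseline. If a correlation exceeds 0.6, two-way repeated ANOVA with Bonferroni adjustment replaces the MANOVA.

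The section Hypotheses of the study gives two explanatory hypotheses for the MBCT arm. The first expects "positive correlations between the levels of mindfulness of the caregivers (total score of five facets of mindfulness) and the improvement in their stress" and in other outcomes. The second links increased use of mindfulness facets to improvement in psychological outcomes. The planned correlation takes "The FFMQ total score as the independent variable and the outcome measurements including mean scores of stress, depression, burden, and anxiety" as its variables, that is, scores and not changes.

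Under Limitations, after noting possible bias because participants know their intervention, the article says that "the level of mindfulness will be measured to understand the mediating effect or active components of the MBCT".

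**The concern.** Data collection and analysis do not match. A between-group or group × time effect needs the variable in both groups, and a time factor starting at T0 needs a T0 value. The FFMQ has neither.

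Two consequences could reach beyond the FFMQ. First, in a joint multivariate model a variable that is wholly absent in one arm can remove that arm from the analysis of every other outcome, including the primary one. Second, the FFMQ takes part in the rule that selects the main model, through a baseline correlation for which no true baseline FFMQ exists. If this is noticed only at analysis, the workaround for the primary outcome's model would be chosen after the data are in.

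The explanatory analyses have a related problem. Correlating score levels with score levels does not address a hypothesis about improvement: a more mindful caregiver may simply be a less stressed one, with or without an intervention effect. And the mediating effect, offered in response to the lack of participant blinding, rests on a contrast that will not be observed.

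**Working it through.** **Inputs.** 50 participants per group (Sample size); three occasions, T0, T1 and T2 (Data analysis plan); FFMQ in the MBCT arm only, first at the end of session 3 of 7 (Outcome measurement). The plan gives no figure for the FFMQ to reproduce.

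**1. Is the group × time model estimable for the FFMQ?** With G = 1 for MBCT and 0 for SIRE, and indicators t1, t2 for the later occasions:

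E[FFMQ] = b0 + b1·G + b2·t1 + b3·t2 + b4·G·t1 + b5·G·t2

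Only MBCT is observed, so G = 1 in every row. The G column then equals the intercept, and the two interaction columns equal t1 and t2. Only the sums b0 + b1, b2 + b4 and b3 + b5 are identified.

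| FFMQ collected in | Columns | Rank | Group effect | Interaction |
|---|---|---|---|---|
| MBCT only (50 × 3 readings) | 6 | 3 | not estimable | not estimable |
| Both arms (100 × 3 readings) | 6 | 6 | estimable | estimable |

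The rank of 3 already lets the session-3 reading stand in for T0. If T0 is taken literally, only T1 and T2 remain and the rank is 2.

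**2. Do the plan's other provisions repair this?**
- The ANOVA fallback does not: a two-way ANOVA of the FFMQ has the same empty arm.
- LOCF does not: controls have no earlier FFMQ value to carry forward.
- Multiple imputation does not: no control FFMQ is observed, so the data carry no information on the arm difference.

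**3. What happens to the other outcomes?** In one joint MANOVA with complete-case handling, participants with all variables number 0 of 50 in SIRE and at most 50 of 50 in MBCT. The control arm's PSS data go with it. With separate models per outcome, or the FFMQ left out, nothing is lost for PSS.

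**4. The baseline correlation check.** The FFMQ entry would pair outcomes measured before treatment with an FFMQ reading taken after 3 of 7 sessions, in at most 50 of the 100 participants. A correlation above 0.6 in that pairing would switch the main model for all outcomes.

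**5. The explanatory hypotheses.**

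| | Hypothesis | Planned correlation | Can the data give what is hypothesised? |
|---|---|---|---|
| 1 | FFMQ level with improvement | FFMQ score with mean outcome score | Yes, within MBCT: outcomes exist at T0, T1 and T2 |
| 2 | Increased use of facets with improvement | Facet score with mean outcome score | In part: FFMQ change only from session 3, outcome change from T0 |

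These within-arm correlations have limited reach. By the Fisher z approximation at 80% power and two-sided 5%, the smallest detectable correlation is r = tanh[(1.96 + 0.84)/√(n − 3)]. For n = 50 this is tanh(2.80/√47) ≈ 0.39; for n = 45 (10% attrition) it is tanh(2.80/√42) ≈ 0.41.

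**6. Mediation.** The first step is the effect of allocation on the mediator, mean FFMQ in MBCT minus mean FFMQ in SIRE. The second term is never observed.

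**The case against.** The strongest reply is that the FFMQ is a process indicator, that the late first reading is openly stated and reasoned, and that both explanatory hypotheses concern changes within the MBCT arm, for which one-arm measurement is suitable. Much of this stands, and it rules out several stronger readings.

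- A reader might infer that the hypotheses cannot be tested at all. That goes too far. Hypothesis 1 can be computed within MBCT as it is worded. Hypothesis 2 can be examined as change from session 3. The defect is that the analysis section plans something else.
- A reader might infer that the main analysis necessarily loses all controls. That requires a joint model containing the FFMQ and complete-case handling. The article implies the first by listing the FFMQ with the outcomes, but it does not spell out either. All seven efficacy outcomes are collected in both arms.
- A reader might turn 3 of 7 sessions into a 43% loss of the mindfulness gain. Sessions are not gain. The article cites evidence that the rise starts after the mid-point, and nothing in it lets us size what is missed. What can be said is that any earlier gain goes unmeasured.
- A reader might count outcomes missing from the correlation list: four are named, against seven in hypothesis 1 and six in hypothesis 2. The list is introduced as inclusive, so it need not be complete, and a condensed article may shorten it.
- Mediation appears in a single sentence under Limitations, which also offers active components as an alternative aim. No mediation model is planned, and within-arm correlations with facets and practice time can speak to active components descriptively.

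What the reply does not answer is the contradiction itself. The reason given for the late reading supplies neither a control value nor a T0 value. Nor is this a detail left to an unseen analysis plan: the article explicitly puts the FFMQ in the between-group model and in the baseline check.

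**Conclusion.** The concern holds for the FFMQ's place in the analysis. As written, no FFMQ group or group × time effect is estimable (3 of 6 parameters identified, with 0 of 50 controls measured). No T0 FFMQ exists for the time factor or for the check that chooses between MANOVA and ANOVA. The planned level-to-level correlations do not match hypotheses about improvement, and a mediating effect cannot be estimated from one arm.

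The effect on the primary outcome is conditional. All controls drop out only if the FFMQ enters one joint complete-case MANOVA; kept out of it, the PSS comparison is untouched. The documents therefore do not support a conclusion that the trial cannot answer its primary question, nor that the one-arm FFMQ data are useless. These conclusions rest on the stated 50 per group and on the FFMQ being collected exactly as described under Outcome measurement.

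**What to change.** 1. Remove the FFMQ from the between-group MANOVA and its ANOVA fallback, and from the baseline correlation check. Analyse it over time within MBCT only, calling the first reading a session-3 value and not a baseline.
2. Replace the correlations with mean scores. For hypothesis 1, relate FFMQ level to baseline-adjusted change in the outcomes that hypothesis names. For hypothesis 2, relate FFMQ change (total and facets) to baseline-adjusted change in the outcomes it names, labelled as change from session 3 unless a T0 value exists.
3. Reword the Limitations sentence to an association within the MBCT arm. Alternatively, where still possible, give the FFMQ-SF to both arms at visits already held: at T0 for those not yet randomised, otherwise at T1 and T2.

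Items 1 and 2 and the rewording in item 3 cost only text and should be settled before the data are analysed. Collecting the FFMQ-SF in controls costs a short amendment and a small respondent burden. Because recruitment began in May 2018, with the trial due to end in May 2019, a reading before randomisation may already be out of reach for many participants, so the textual corrections should not wait for it.

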### Primary outcome measure

#### Perceived Stress Scale (PSS)

The participants’ perceived stress will be measured with the Chinese version of the PSS [30], which was developed to measure the degree to which situations in one’s life are appraised as stressful [31]. It was used to measure the stress levels in the pilot study. It contains 10 items with a five-point Likert-type scale rating from 0 (never) to 4 (very often). The Chinese version of the PSS was tested in 1800 adults living in the community in Hong Kong [30]. The results showed acceptable levels of psychometric properties which included internal consistency Cronbach’s alpha of 0.85 and a test-retest reliability coefficient 0.85 [30, 32].

### Secondary outcome measures

Previous literature shows that MBCT has a positive effect on several health-related outcomes such as depression, anxiety, and quality of life, and our prior feasibility study also found preliminary effects on the burden and the stress-managing strategies in the family caregivers of PWD [33]. Therefore, the below secondary outcomes were selected.

#### Zarit Burden Scale (ZBI)

Caregiver burden of the participants will be measured with the Chinese version of the ZBI [34]. ZBI was designed to assess the subjective burden of caregivers, defined as the extent to which caregivers perceived their emotional or physical health, social life, and financial status to have changed as a result of caring for their relative with dementia [35]. It comprises 22 items, including factors most frequently mentioned by caregivers as problem areas such as caregivers’ health, psychological well-being, finances, social life, and the relationships between the caregiver and the patient with dementia. It was translated into Chinese in 2005 and test-retest reliability was 0.99 and the split-half correlation coefficient was 0.81 [34]. The correlation between the ZBI and the General Health Questionnaire was 0.59 and 0.57 with the Activity Survey.

#### Center for Epidemiologic Studies Depression Scale (CESDS)

The participants’ depression will be measured with the Chinese version of the CESDS [36], which is a self-reported measure of depression containing 20 items [37]. It measures the common symptoms of depression in terms of depressed mood, feelings of guilt and worthlessness, and feelings of helplessness. The scores range from 0 to 60 and higher CESDS scores indicate increasing levels of depression. The Chinese version of CESD was tested in the community with 3686 Chinese adults attending primary care services [36]. The results showed acceptable levels of psychometric properties which include a test-retest reliability of 0.91 and internal consistency for general depression of 0.86.

